### Interim analyses {21b}

No interim analyses are planned.

### Methods for additional analyses (e.g. subgroup analyses) {20b}

Analyses will be performed in the NIV and invasive ventilation subgroups, in the pneumonia subgroups (yes/no), and in the subgroups of patients who received/not corticosteroids in the last 48 h before randomization (prespecified in the analysis plan) to assess the homogeneity of the difference between the two treatment groups. These subgroup analyses will be supplemented by interaction tests between the treatment and the subgroup variables using Breslow & Day tests. The results will be graphically presented using Forest plots.

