**Methods and analysis:**

This study is an investigator-initiated, multicentre, randomized, placebo-controlled, double-blind trial comparing systemic corticosteroids to placebo during severe acute exacerbations of COPD in patients who require mechanical ventilation in French ICUs. A total of 440 patients will be randomized 1:1 to methylprednisolone (1 mg/kg) or placebo for 5 days, and stratified according to initial mechanical ventilation (non-invasive or invasive), pneumonia as triggering factor, and recent use of systemic corticosteroids (< 48 h). The primary outcome is the number of ventilator-free days at day 28, defined as the number of days alive and without mechanical invasive and/or non-invasive ventilation between randomization and day 28. Secondary outcomes include non-invasive ventilation (NIV) failure rate, duration of mechanical ventilation (invasive and/or NIV), circulatory support (vasopressor), outcomes related to corticosteroid adverse events (severe hyperglycaemia, gastrointestinal bleeding, uncontrolled arterial hypertension, ICU-acquired weakness, ICU-acquired infections, and delirium), lengths of ICU and hospital stay, ICU and hospital mortality, day 28 and day 90 mortality, number of new exacerbation(s)/hospitalization(s) between hospital discharge and day 90, and dyspnoea and comfort at randomization, ICU discharge, and day 90. Subgroup analyses for the primary outcome are planned according to stratification criteria at randomization.

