### Outcomes {12}

#### Primary outcome measure

Number of ventilator-free days (VFDs) at day 28 is defined as the number of days alive without mechanical ventilation (invasive and/or NIV) between randomization and day 28.

VFDs are defined as follows:VFDs = 0 if the patient dies before 28 days or the patient requires mechanical ventilation for ≥ 28 daysVFDs = 28 − x if the patient is successfully weaned from mechanical ventilation within 28 days, where *x* is the number of days spent receiving mechanical ventilation (invasive and/or NIV).

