## Statistical methods

### Statistical methods for primary and secondary outcomes {20a}

All analyses will be performed by the study statistician according to a predefined statistical analysis plan, using the latest versions of R software© (R Foundation for Statistical Computing, Vienna, Austria) or Statistical Analysis System© (SAS). A two-tailed *p* value of less than 0.05 will be considered as indicating statistical significance.

In accordance with the CONsolidated Standards Of Reporting Trials (CONSORT) statement, a flow diagram will describe the progress of patients in the two groups through the phases of the trial (enrolment, intervention allocation, intervention received, follow-up and data analysis). The analysis will be performed on an intention-to-treat basis. In case of premature stop or withdrawal from the study, patients will not be substituted. Missing values will be described and, according to nature and frequency, multiple imputation methods will be used. A per-protocol analysis will be used as a sensitivity analysis, excluding patients who were wrongly randomized or did not receive the allocated intervention. Comparative analysis will systematically be done with (main analysis) and without adjustment on randomization stratification factors.

Quantitative data will be described as means, medians, standard deviations, and interquartile ranges. Nominal data will be described as percentages with 95% confidence intervals. Proportions of missing data will be given. Patient characteristics will be described by centre and compared. Quantitative data will be compared using *t*-tests or non-parametric tests (Mann–Whitney sum rank) when the distribution does not approach symmetry even after suitable transformation (Tukey’s ladder of powers). Qualitative data will be compared by means of chi-square tests or Fisher exact tests. Time-to-event data (survival) will be described using Kaplan–Meier curves.

The analysis of the primary outcome (i.e., distribution of VFDs that is highly skewed) will be performed by a multivariate non-parametric test, taking into account stratification and minimization criteria used in the randomization [21]. The final test will be performed at a 0.049 two-sided alpha risk to guarantee a global 5% alpha level.

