The main analysis will be performed according to the intention-to-treat principle on the full dataset, while analyses on imputed data dealing with missingness will be considered as sensitivity analyses. As a secondary analysis, a time-to-event model, where death and becoming ventilator free are competing risks, with a fixed factor corresponding to the randomization arm, centre being considered as a random factor, taking into account other prognostic factors and their interactions with the randomized treatment, will be developed.

The analysis of the effect of the intervention on secondary criteria: mortality, adverse events, and length of ventilation, will be performed using generalized linear model regression. The link function and distribution of errors will be chosen according to the nature of the response: logistic and binomial if the response is binary (mortality), identity and Gaussian if the response is considered continuous. Time-to-event censored data (becoming ventilation free or death being competing risks) will be analysed by piecewise exponential regression models. The main secondary analyses will firstly be stratified on randomization criteria without further adjustment then, after bivariate screening, the main confounders (*p* value < 0.2 or retrieved from the literature) and interactions with treatment will be tested in a multivariable model. The shape of the relationship of continuous factors will be explored by fractional polynomials. Goodness-of-fit will be verified (influential observations, R2, discrimination, calibration) and performance of the models will be assessed by Akaike information criteria.

These analyses will be performed on the intention-to-treat groups, except for safety or tolerability criteria, which will be analysed on per-protocol populations.

Analyses will be performed in the NIV or invasive ventilation subgroup (prespecified in the analysis plan) to assess the homogeneity of the difference between the two treatment groups. These subgroup analyses will be supplemented by interaction tests between the treatment and the subgroup variables using Breslow & Day tests. The results will be graphically presented using Forest plots.

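### The Breslow-Day interaction test named for the subgroup analyses does not match ventilator-free days, and the protocol defines no dichotomy of that score

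*Protocol article*

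**What the plan says.** - **Outcome of the subgroup analyses.** The Abstract (Methods and analysis) states: "Subgroup analyses for the primary outcome are planned according to stratification criteria at randomization".
- **Scale of that outcome.** Primary outcome measure defines VFD-28 as "the number of days alive without mechanical ventilation (invasive and/or NIV) between randomization and day 28". It is 0 for death before 28 days or for ventilation lasting 28 days or more, and otherwise 28 minus the days ventilated.
- **Its primary analysis.** Section {20a} refers to the "distribution of VFDs that is highly skewed" and says that the analysis "will be performed by a multivariate non-parametric test" that takes the stratification into account. Sample size {14} also rests on a Wilcoxon test of VFD.
- **Interaction test.** Section {20b} lists three pairs of subgroups (ventilation mode, pneumonia, recent corticosteroids) and adds: "These subgroup analyses will be supplemented by interaction tests between the treatment and the subgroup variables using Breslow & Day tests". Section {20a} gives the same instruction for ventilation mode: "interaction tests between the treatment and the subgroup variables using Breslow & Day tests".
- **Binary outcomes.** For secondary criteria, section {20a} sets the regression model by type of response: "logistic and binomial if the response is binary (mortality), identity and Gaussian if the response is considered continuous".

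**The concern.** Breslow-Day takes one 2x2 table (arm by a yes/no outcome) for each level of the subgroup variable and asks whether the odds ratio is the same in each. VFD-28 is not a yes/no outcome, and nowhere does the protocol turn it into one. The named test and the named outcome therefore do not fit together.

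A statistician following the text has two ways out, and neither is described. One is to choose a cut on VFD-28 and run the test. The interaction is then judged on an odds ratio at that cut, while the treatment effect itself is judged on the whole distribution. The other is to use a different test, which departs from the protocol.

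What is at stake is how the subgroup results are read. Section {16a} explains that pneumonia was made a stratification factor because it may alter the benefit of corticosteroids, so readers will look at whether the effect differs between these subgroups.

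**Working it through.** The protocol gives no figure for the interaction tests, so there is none to reproduce. The check matches the scale of the outcome to the data that the test needs, then illustrates what follows if the outcome is forced into that form.

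**1. What the test needs.** For strata k = 1, ..., K, let a(k) be the number of treated patients with the event. Breslow-Day sums [a(k) − E(a(k))]² / Var(a(k)) over the strata, with E and Var computed under a common odds ratio, and refers the sum to chi-square with K − 1 degrees of freedom. Each subgroup variable here has two levels, so K = 2 and there is 1 degree of freedom. Every quantity in the formula is a count of a binary event.

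**2. What the outcome supplies.** VFD-28 is a count from 0 to 28. In one simulated trial of 200 per arm it took 24 distinct values. A count a(k) exists only after a rule of the form VFD ≥ c is imposed, and the protocol gives no c.

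**3. Dependence on the cut, in that one simulated trial.**

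Inputs from Sample size {14}: 75% NIV and 25% invasive; overall mortality 17%; mean duration 5.8 days and median 4, hence log-normal sigma = √(2 ln(5.8/4)) = 0.862.

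Assumed inputs, chosen to agree with those totals:
- control mean 5 days (NIV) and 8.2 days (invasive): 0.75 × 5 + 0.25 × 8.2 = 5.8
- mortality 13% and 29%: 0.75 × 13% + 0.25 × 29% = 17%
- a 2-day benefit in NIV patients only

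| Test of treatment by ventilation mode | p |
|---|---|
| Breslow-Day, VFD ≥ 1 | 0.33 |
| Breslow-Day, VFD ≥ 14 | 0.12 |
| Breslow-Day, VFD ≥ 20 | 0.09 |
| Breslow-Day, VFD ≥ 22 | 0.32 |
| Breslow-Day, VFD ≥ 24 | 0.16 |
| Breslow-Day, VFD ≥ 25 | 0.008 |
| Breslow-Day, VFD ≥ 26 | 0.024 |
| Interaction term on ranked VFD, no cut | 0.016 |

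The same data fall on either side of 0.05 depending on c. This is one dataset. It shows that the cut matters, not how often the conclusion would change.

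**4. Are the two approaches testing the same thing?** Repeated simulation compared a rank-scale interaction with a test of equal odds ratios at a cut of 24 (2,000 trials per scenario; 330 NIV and 110 invasive patients; mortality assumed 12% and 32%, which again averages 0.75 × 12% + 0.25 × 32% = 17%). The effects are assumptions throughout.

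| Assumed mean duration, placebo to corticosteroid | Rank interaction rejects | Cut at 24 rejects |
|---|---|---|
| NIV 5 to 3; invasive 8.2 to 11 (crossover) | 77% | 67% |
| NIV 5 to 3; invasive 8.2 in both arms | 50% | 34% |
| NIV 5 in both arms; invasive 8.2 to 5 | 22% | 33% |
| Same 40% reduction in both subgroups | 11% | 4% |

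The ordering reverses in the third row. In the last row one test rejects near the nominal 5% and the other more often, because no interaction on one scale need not mean no interaction on another. The two tests have different null hypotheses.

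**The case against.** The strongest reply is that neither sentence naming Breslow-Day names an outcome. In section {20a} the sentence follows paragraphs on secondary criteria that include mortality and adverse events, where the test is valid, so it may be generic wording. That is fair as far as it goes. But the Abstract ties the subgroup analyses to the primary outcome, and section {20b} lists exactly the three stratification factors. Even on the generous reading, the text then gives no interaction test for VFD-28.

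A second reply is that the SAP may settle it. What the SAP says is unknown, but the protocol is not silent: it names a specific test, twice, that does not fit. An SAP that follows it must add a dichotomy, and one that does not must depart from it.

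Several stronger readings are tempting, and the documents do not support them:

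- **That the test is impossible to run.** It runs on a dichotomised VFD. The defect is that no dichotomy is defined and the effect measure changes.
- **That these are the trial's only planned looks at effect modification.** Section {20a} also plans treatment interactions in the competing-risks model and in the multivariable models for secondary outcomes. It does not name the three stratification factors for those terms, so they soften the problem without curing it.
- **That a cut would be picked after seeing the data.** Nothing says so. Section {20a} commits to a predefined analysis plan.
- **That power is lost in general.** The third scenario above shows a gain from dichotomising.
- **That a subgroup test is invalid unless adjusted for the other stratification factors.** It is not. Adjustment is preferable here because section {20a} makes the adjusted comparison the main one.

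**Conclusion.** The point holds as a mismatch between the named test and the named outcome. It rests on the protocol's text and on what Breslow-Day computes, with one inference: that the Abstract's sentence fixes the outcome for sections {20a} and {20b}. It does not rest on the simulations, which illustrate cut-dependence under assumed subgroup means, mortalities and effects and do not predict what this trial would show.

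The reach is limited. The interaction tests supplement the subgroup analyses. The primary test, its estimate, the sample size and the safety analyses are unaffected. This should be corrected before the analysis, but it does not threaten the trial's main conclusion.

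**What to change.** In sections {20a} and {20b}, replace Breslow-Day for VFD-28 with a treatment-by-subgroup interaction suited to an ordinal or skewed score, adjusted for the stratification factors. Acceptable choices are a rank-based or probabilistic-index interaction, which stays closest to the planned non-parametric test, or a proportional-odds model. The latter adds an assumption that should be checked, since deaths pile up at 0. Name one.

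In the forest plot that is already planned, show for each subgroup the effect estimate and 95% confidence interval on the same scale as the interaction test. Keep Breslow-Day only for binary outcomes such as mortality, and say so.

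The cost is a wording change in the protocol, matching text in the SAP and a few lines of code. Conduct, data collection and sample size do not change.

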### Methods in analysis to handle protocol non-adherence and any statistical methods to handle missing data {20c}

The trial will follow the modified intent-to-treat principle as defined above, so we will not exclude data from the database in case of intervention discontinuation. We will follow the participants who discontinue the intervention during the study duration, unless the participant asked not to be followed.

### Patient and public involvement {31c}

Patients and the public were not involved in the study design. Participants will be able to have access to the findings of the study on reasonable request.

Data are available on reasonable request. The procedures carried out with the French data privacy authority (Commission Nationale de l'Informatique et des Libertés) do not provide for the transmission of the database, nor do the information and consent documents signed by the patients. Consultation by the editorial board or interested researchers of individual participant data that underlie the results reported in the article after deidentification may nevertheless be considered, subject to prior determination of the terms and conditions of such consultation and in respect for compliance with the applicable regulations.

### Composition of the data monitoring committee, its role and reporting structure {21a}

Although both strategies (corticosteroid treatment or no corticosteroids) are currently used in routine practice, a data safety monitoring board (DSMB) was involved to ensure the safety of the patients participating in this research. The members of the DSMB will not otherwise be involved in the study. They will be appointed for the duration of the study and will undertake to participate and respect the data confidentiality. The DSMB will only have an advisory role. They will meet—as required by the trial sponsor and at least once after the inclusion of the first 50 patients and once after the inclusion of the first 200 patients—to analyse tolerance and adverse events that occur during this trial and will decide what action to be taken, if any.

The members of the DSMB are as follows: [name]-PhD (ICU, Hôpital Saint-Louis, Paris, France), [name]-PhD (ICU, Hôpital Tenon, Paris, France), [name]-PhD (Pulmonology, Hôpital Cochin, Paris, France), and [name]-PhD (Biostatistics, Hôpital Saint-Louis, Paris, France).

### Adverse events reporting and harms {22}

Included patients will be monitored closely for clinical (daily) and biological (as appropriate in routine practice) monitoring to ensure accurate assessment of the safety of the study. Serious adverse events (SAEs) will be collected throughout the study and during the 20 days after the last experimental treatment injection. The DSMB will be regularly informed of all SAEs.

Corticosteroids have been widely used worldwide in numerous medical indications for decades. Therefore, the adverse events related to corticosteroids are well known and expected in the vast majority of cases.

Any SAE, regardless of its causal relationship to the research (except those identified in the protocol as not requiring immediate reporting), must be reported to the sponsor.

Any SAE must be declared to the study sponsor as soon as the investigating physician becomes aware of it. The initial declaration may be followed by additional information within 8 days in the event of a fatal or life-threatening event and within 15 days in other cases. The investigator is responsible for noting and reporting all SAEs (apart from the exceptions prespecified list) that occur during the entire study, from the date of signed consent and throughout the participant’s follow-up period. Moreover, regardless of the time after the study end, any SAE that may be due to the research must be declared to the sponsor if no other cause than the research can reasonably be attributed.

Each SAE will be described on the appropriate form in an attempt to be as exhaustive as possible.

If an adverse event occurs, the investigator can either continue the assigned treatment or temporarily or permanently withdraw it. In addition, surveillance will be strengthened, and a symptomatic product can be added.

### Frequency and plans for auditing trial conduct {23}

The sponsor has scheduled regular monitoring by a dedicated research technician to ensure the proper conduct of the study. The timing of the monitoring will consist of one visit (2 days) per centre every 3 months.

### Plans for communicating important protocol amendments to relevant parties (e.g. trial participants, ethical committees) {25}

Any modifications to the protocol that impact the conduct of the study, the potential benefit to the patient, or that may affect patient safety—including changes to the study objectives, study design, patient population, sample sizes, study procedures, or significant administrative aspects—will require a formal amendment to the protocol. Such amendment will be submitted to the Comité de Protection des Personnes Ouest 6 (Brest, France).

Important protocol changes, as well as changes in eligibility criteria, outcomes, or analyses, will be communicated to the investigators, institutional ethics committee, trial participants, and trial registries.

### Dissemination plans {31a}

Findings will be published in peer-reviewed journals and presented at national and international meetings. Communications, reports, and publications of the study results will be placed under the responsibility of the principal coordinating investigator of the study and the steering committee. Reporting will follow the CONSORT statement and rules of publication will follow the international recommendations according to The Uniform Requirements for Manuscripts (International Committee of Medical Journal Editors, April 2010).

## Discussion

To date, there have been no conclusive randomized controlled trial on the benefits of corticosteroids for patients with COPD during severe acute exacerbations requiring mechanical ventilation (invasive or NIV) in the ICU [10–12]. International guidelines that recommend corticosteroids relying on a previous study with a small sample of non-ICU patients and heterogenous results [10]. Severe COPD exacerbations are still an important medical burden and the routine use of NIV in the 1990s improved survival [22]. Since then, the ICU mortality rate has remained stable (15%) [3]. Decreasing the duration of mechanical ventilation and avoiding the need for invasive mechanical ventilation are associated with better outcomes and are of high interest in the ICU. Symptomatic therapies during COPD exacerbations are limited [10]. Among the numerous factors associated with NIV failure or delayed weaning from invasive mechanical ventilation, the roles of persistent airway inflammation and bronchial spasm have been highlighted, and these could be reduced with systemic corticosteroids. However, their benefit is still a matter of debate and there is a lack of evidence [11, 12]. We expect our study to add a significant contribution regarding the benefits of corticosteroids for patients with COPD. Of note, the numerous adverse events associated with corticosteroids are not without consequences for frail patients and could impact prognosis, e.g. hyperglycaemia, intestinal haemorrhage, uncontrolled arterial hypertension, ICU-acquired weakness, and ICU-acquired infection. The study will therefore pay special attention to these adverse events.

Overall, we hope that this trial will help to revise international recommendations with a high level of evidence for patients with severe acute COPD exacerbation requiring NIV or invasive mechanical ventilation in the ICU.

## Trial status

The current version of the protocol is Version 5.0, November, 3, 2022.The first patient was included in the study on October, 21, 2021.The recruitment period is 24 months (2 years).

